### Recruitment plan and expected participant timeline

The project is estimated to run over a 5 years period (2015–2019). During the project period an estimated 17.600 mother-infant dyads will be screened by community health nurses using two standardized screening instruments:The Alarm Distress Baby Scale (ADBB) in detecting infant social withdrawal at 2, 4 (only first time mothers) and 8 months With a cut-off score of 4/5 and an expected prevalence of 4% [22] we expect the nurses to identify 704 infants scoring above cutoff during the project period. We expect that up to half (*n* = 352) of these families will refuse to be referred to the project, and/or will fulfill exclusion criteria (e.g. mother does not understand and speak Danish, the mother has psychotic symptoms etc.).The Edinburgh Postnatal Depression Scale (EPDS) in detecting maternal postnatal depression 2 months postpartum. With a cut-off score of 10/11 and a point prevalence of 5.5% [108] we expect the nurses to identify 968 mothers with depressive symptoms. Again, we expect that up to half (*n* = 484) of the families will refuse to be referred to the project and/or fulfill exclusion criteria.

Confirmation of infant social withdrawal and depression status will be conducted by clinical psychologists during a home visit (T0) 10–20 days after the health nurses’ screening.

In total, we expect that 704 families agree to be referred. Of these families, we expect that up to 25% will decline to participate either after being contacted or during baseline assessments. Moreover, for up to 41% of the families, we expect that inclusion criteria will not be fulfilled/exclusion criteria will be fulfilled at T0 (e.g. the mother does not meet criteria for major depressive episode, infant social withdrawal is not confirmed, mother fulfill criteria for bipolar disorder etc.) See Fig. 1.

**Fig. 1 Fig1:**
[figure not shown]
Enrollment chart for CIMHP

A sample of an estimated 113 eligible parent (s) from the ADBB screening and an estimated 201 eligible parent (s) from the EPDS screening will enter into the clinical, randomized controlled trial to test the efficacy of the group counseling program (COS-P) compared to Care as Usual (CAU). Intake to the RCT will stop when the sample of 314 has been enrolled (see enrollment chart, next page). We aim for 250 families to complete the follow-up (see sample size).

### Randomization

Allocation ration is 2:1 to either COS-P or CAU. For allocation of participants, a computer-generated list of random numbers is used. The list is created using block randomization with random block sizes of 2, 4, or 6. The allocation sequence is generated by an investigator with no clinical involvement in the trial, Associate [name] (TL) and stored in a password-protected electronic document accessible only by TL.

To enter a family into the study, the psychologist who conducts baseline assessments and enroll the families into the trial will open an opaque and sealed envelope containing a card with details of with intervention group the family is randomized to as well as an randomization number. This envelope is prepacked by an assistant with no affiliation to or knowledge about the project who receives the allocation sequence from TL and numbers 450 envelopes sequentially. The packed envelopes are stored with the project coordinator of UCPH BabyLab, to whom the allocation sequence is thus concealed.

When a family is referred to the study by a health nurse, the project coordinator who schedules a home-visit will provide the psychologist with the next consecutively numbered envelope to bring to the visit. To prevent subversion of the allocation sequence, the lab-coordinator will write the name and date of birth of the child on the envelope when a visit is scheduled, and a video-recording is made of the sealed envelope with participant details visible. A second researcher will later view the recordings to ensure envelopes are still sealed when participants’ names are written on them. If a family is not included during the home-visit, the envelope is given back to the lab-coordinator who will store all none-opened envelopes, and the randomization number is not used. Unused envelopes are not reused purely for logistic reasons.

### Statistical methods

The analysis of both primary and secondary endpoints will be conducted under the intention to treat principle. However, as a supplement we will also conduct analyses where the actual treatment participation is taken into account. Intuitively the first analysis provides as lower bound for the effect of the COS-P treatment (as it evaluates a likely unfavorable condition) while the second analysis provide an upper bound (as it evaluates a likely favorable condition). If more than 95% observations are complete we will only conduct a complete case analysis. Otherwise multiple imputation will be used to handle missing data. Imputations will be conducted using the software package REALCOM [109], which includes an extension of the chained-equation technique to clustered data.

The primary comparison of COS-P and CAU is conducted using linear regression of maternal sensitivity at T1 on treatment group adjusted for baseline maternal sensitivity. Generalized estimating equations (GEE) will be employed to account for the correlation induced by mothers attending the same group in the COS-P arm, the same therapist treating several mothers, and similar in the CAU group. A two sided test with a 5% significance level will be employed. When estimating the effect size the model will further be adjusted for a) the T0 values of maternal sensitivity and b) the family characteristics mentioned above; Both will be reported but the value a will be considered the important. To assess the degree to which the treatment effect is diluted by the inclusion of non-completers (mothers participating in 4 or fewer sessions) we will repeat the analyses above, but excluding non-completers from the COS-P group.

Secondary endpoints where a baseline value is available will be analyzed in the same way as the primary endpoint, see above. Binary outcomes will be analyzed by logistic regressions and continuous outcomes by linear regressions. For secondary endpoints where no baseline is available the analyses will only be adjusted for the family characteristics mentioned above. GEE techniques will be used throughout Significance will be assessed both using a 5% significance level and adjusted for multiple testing (6 tests planed) by the Holm–Bonferroni method. Findings significant even after correcting for multiple testing will be treated as truly significant findings while findings with *p*-values below 5%, but not significant after correcting for multiple testing will be described as potential significant findings.

The final secondary endpoint on heterogeneity of effects of COS-P across family types will be assessed by including an interaction term between group membership and family type (family types are: 1) Infant socially withdrawn; 2) Infant socially withdrawn AND maternal depression; and 3) Maternal depression only in the linear regression planned for the primary analysis.

For both logistic regressions and linear regressions model fit will be assessed by graphical procedures. In case of poor model fit additional sensitivity analyses and bootstrap procedures will be employed to establish if the findings of the study are sensitive to the lack of model fit. A detailed statistical analysis plan will be completed before half of the intended sample size has been recruited.

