### Interventions

#### Circle of security-parenting (COS-P)

The COS-P manual and video material has been translated to Danish (Tryghedscirklen – Forældreprogrammet, manual, Lier, 2013). Based on standard video material of parent-infant interactions, parents are trained to see and understand infant attachment behavior and especially to learn about infant miscuing attachment signals. In the COS-P intervention graphics and video illustrations is designed in a pedagogical form with the aim of meeting the variability of participants in motivation, requirements, openness and compliance with treatment. In the current study, the intervention consists of 10 weekly 90 min sessions, as more time is spend on chapter three and five in the COS-P manual. Both mother and her partner are invited to participate and each group includes 5–7 families. Child minding facilities are provided during the sessions. The families who are allocated to the COS-P intervention are not excluded from receiving other treatment, for example antidepressant medication, psychotherapy, and/or CAU as well. If a COS-P family experiences a crisis they may be offered extra home visits by the health nurse. The health nurse of the family remains to be the primary responsible person of the family and she will by default continue to pay both the COS-P and CAU families the routine health visits.

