### Care as usual (CAU)

The existing standard practices for infants and families at risk in Copenhagen will be the active control condition. These vary in content and duration in the districts of Copenhagen. Likewise, CAU may change during the project period. At project start all districts offered (a) group interventions for mothers who experience postnatal depressive symptoms and/or (b) extra counselling home-visits by a health nurse. Number and content of extra home-visits vary in accordance with the families’ specific needs, but rarely exceed 12 extra visits per year. Furthermore, all districts also have offers to families who experience different kinds of parenting difficulties (not specified) in the postpartum period. For example, The Incredible Years, Parents and Babies®, a group-based 10-session intervention for mothers and infants, and individual MARTE-MEO® intervention. Finally, the nurses can refer the family to anonymous counselling provided by the local social security services (“Anonym rådgivning, Familiehuset, Socialforvaltningen”).

When a family is allocated to CAU, UCPH Babylab informs the nurse who referred the family to the project, and she contacts the family and discusses with the family what type of CAU intervention is appropriate for the family. Every third months, staff from Babylab will contact the health nurses who have families referred to the CAU-group to monitor the CAU group with respect to what specific CAU intervention the families have been offered, compliance, drop-out rates etc.

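### Calling intention to treat a lower bound and the participation analysis an upper bound is not justified, because non-completers are dropped from COS-P only

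*Protocol article*

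**What the plan says.** All of this is in the protocol article, Statistical methods, unless another section is named.

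- The main analysis: "The analysis of both primary and secondary endpoints will be conducted under the intention to treat principle".
- The addition: "as a supplement we will also conduct analyses where the actual treatment participation is taken into account".
- The interpretation of the first: "Intuitively the first analysis provides as lower bound for the effect of the COS-P treatment".
- The interpretation of the second: "while the second analysis provide an upper bound (as it evaluates a likely favorable condition".
- The only participation analysis that is spelled out is meant to show how far non-completers dilute the effect: "we will repeat the analyses above, but excluding non-completers from the COS-P group". Non-completers are defined by attendance: "non-completers (mothers participating in 4 or fewer sessions". The section on COS-P states that "the intervention consists of 10 weekly 90 min sessions", so a non-completer may have attended up to 4 of 10 sessions.
- No matching exclusion is planned in CAU. The Care as usual section says that staff will contact the health nurses "to monitor the CAU group with respect to what specific CAU intervention the families have been offered, compliance, drop-out rates etc", but the analysis does not use this information.

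The section states no assumption under which either bound would hold.

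**The concern.** Attendance is observed after randomization and only in COS-P. Once poor attenders are removed from that arm, the remaining COS-P mothers are compared with a CAU arm that still contains mothers of the type who would not have attended. The difference then combines a treatment effect with a difference in prognosis, whose sign is not known in advance.

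The bound sentence is a rule of interpretation fixed before the data. A reader who accepts it will treat the two estimates as a bracket around the effect of COS-P. One end of that bracket can be produced by selection alone, and the true effect can lie outside it. The exclusion analysis also fails its own stated purpose, because its distance from ITT is not a measure of dilution.

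**Working it through.** The plan gives no figure for this point, so there is none to reproduce.

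**Notation**
- q: share of mothers who are, or in CAU would have been, non-completers. Randomization makes it equal in both arms on average.
- g: outcome without COS-P in completers minus that in non-completers, after covariate adjustment.
- tau, tau_n: effect of allocation to COS-P in completers and in non-completers.
- The effect to be bounded is read as tau. The plan does not define it.

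**Formulas**
- Let m be the untreated mean in completers. The CAU mean is (1−q)·m + q·(m−g) = m − q·g.
- The mean of COS-P completers is m + tau.
- Exclusion estimate = (m + tau) − (m − q·g) = tau + q·g.
- ITT = (1−q)·tau + q·tau_n.
- Exclusion minus ITT = q·(tau − tau_n + g).

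**Upper bound.** It fails when g < 0. With q = 0.2, g = −0.3, tau = 0.40, tau_n = 0.20:
- exclusion = 0.40 − 0.06 = 0.34
- ITT = 0.8 × 0.40 + 0.2 × 0.20 = 0.36

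The supposed upper bound lies below both the completer effect (0.40) and ITT (0.36).

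**Lower bound.** It fails when tau < tau_n.
- COS-P inferior in attenders: tau = −0.2, tau_n = 0, q = 0.2 gives ITT = −0.16, above −0.20. The plan allows for this case: the test is two-sided, and the Discussion considers that COS-P may prove inferior.
- Non-completers gain more: tau = 0.40, tau_n = 0.60, q = 0.2 gives ITT = 0.32 + 0.12 = 0.44, above 0.40.

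**Dilution.** The difference q·(tau − tau_n + g) contains dilution, q·(tau − tau_n), and selection, q·g. The two estimates cannot separate them.

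**Size under a true null (tau = tau_n = 0)**

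Inputs from the Sample size section: SD 0.9, baseline–follow-up correlation 0.5, 250 dyads analysed. From Randomization: 2:1 allocation. Assumed, since the documents give neither: q = 0.1–0.3, g = 0.3–0.45 points.
- Residual SD = 0.9 × √(1 − 0.5²) = 0.779.
- CAU 83.3; COS-P after exclusion 166.7 × (1−q).
- SE = 0.779 × √(1/83.3 + 1/[166.7(1−q)]); for q = 0.2 this is 0.109.
- Rejection = 1 − Φ(1.96 − bias/SE) + Φ(−1.96 − bias/SE).

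| q | g | bias q·g | rejection at nominal 5% |
|---|---|---|---|
| 0.1 | 0.30 | 0.03 | 5.9% |
| 0.1 | 0.45 | 0.045 | 7.1% |
| 0.2 | 0.30 | 0.06 | 8.5% |
| 0.2 | 0.45 | 0.09 | 13.1% |
| 0.3 | 0.30 | 0.09 | 12.7% |
| 0.3 | 0.45 | 0.135 | 22.7% |

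Clustering is ignored. Positive clustering would enlarge the SE and lower these rates.

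**The case against.** **The analysis is supplementary and the wording is hedged.** ITT is the stated principle for primary and secondary endpoints, and the bounds are introduced as intuitive and likely. This stands. A reader might infer that the primary result is compromised, but its estimate, test and sample size do not depend on the exclusion analysis.

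**Both bounds can hold.** If completers gain at least as much as non-completers (tau ≥ tau_n) and would do no worse untreated (g ≥ 0), then ITT ≤ tau ≤ exclusion estimate. This also stands. A reader might infer that both bounds are false. The documents support only that neither is guaranteed, because the plan does not state these conditions.

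**A reversed gap need not put the exclusion estimate below ITT by q·g.** A reader might infer that it does. That is exact only when tau = tau_n. With tau = 0.40, tau_n = 0, q = 0.2 and g = −0.45, exclusion is 0.31 and ITT is 0.32, a difference of 0.01 and not 0.09. With g = −0.3, exclusion (0.34) stays above ITT (0.32).

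**The size rests on assumptions.** The 13% and 23% rejection rates need the larger gap of 0.45 points (0.5 SD). The planned 20% drop-out includes loss during the intervention, so some non-completers may already be missing from the 250 analysed.

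**Covariates help.** The analyses to be repeated include a version adjusted for family characteristics, which may shrink g. But the plan treats the version adjusted for baseline sensitivity as the important one. At a correlation of 0.5 that covariate explains 25% of outcome variance (0.5²), and neither version removes unmeasured selection.

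**The link is inferred.** The text does not say that the 4-session exclusion is the analysis called an upper bound. It is, however, the only participation analysis specified.

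**A detailed analysis plan is promised.** It may refine the models, but the interpretation rule is already stated in the article and would have to be withdrawn.

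**Conclusion.** The concern holds in a limited form. The lower- and upper-bound statements are not guaranteed, and the only specified participation analysis is selected in one arm, with bias q·g for the completer effect. Its difference from ITT mixes dilution with selection. For assumed q of 0.1–0.3 and g of 0.3–0.45 points, the bias is 0.03–0.135 points, or 7.5% to 34% of the 0.40 effect used for sample size (0.03/0.40 and 0.135/0.40). Rejection of a true null is then about 6% to 23%. These figures rest on assumed q and g, a normal approximation and no clustering. Because the primary ITT inference is untouched, this is a change that should be made, not one on which the validity of the trial depends.

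**What to change.** 1. Delete the sentence that presents the two analyses as a lower and an upper bound.
2. Replace the one-arm exclusion as the participation analysis with a complier-average causal effect. Use randomization as the instrument and attendance at 5 or more sessions as the exposure, with the same covariates and allowance for clustering as in the primary model.
3. State its assumption that allocation to COS-P has no effect in mothers below the attendance cut. If that is wrong, the estimate is off: with q = 0.2, tau = 0.40 and tau_n = 0.20, it would be 0.36/0.8 = 0.45 and not 0.40. Add a version with any session attended as the exposure. This relaxes the assumption but does not test it, and it estimates the effect in a wider group of attenders.
4. If the exclusion analysis is kept, label it descriptive, say that it is not a bound, and do not read its distance from ITT as dilution.

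Cost: a change of wording and one extra model, plus its sensitivity version, on attendance data that the plan already needs. The complier estimate has a wider interval. Steps 1 and 4 alone would remove the wrong interpretation at almost no cost, but would leave no participation analysis protected by randomization.

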### Measures

There are two points of assessments for COS-P and CAU groups: At baseline (T0) when the infant is 2–12 months old and at follow-up (T1), when the infant is 12–16 months. T0 takes place at a visit in the families’ homes. T1 takes place at UCPH Babylab for both COS-P and CAU groups. To promote retention and complete follow-up participants will receive a gift card of 200 DKK when completing follow-up assessments.

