### Background information and control variables

Information about risk condition (infant social withdrawal, maternal depression, or both), infant gender and infant age at referral, as well as parent age, gender, marital status, educational background, employment status, current and lifetime depression status, parental attachment style, personality dysfunctioning, family functioning, alcohol and drug abuse, smoking, parental adverse childhood experiences will be collected through surveys at baseline. Basic background information on eligible individuals who are not enrolled in the study is available from register-based data. Furthermore, we ask decliners about their reason for decline

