### Sample size

Based on a literature review regarding assessment of maternal sensitivity using CIB (Feldman, 1998) conducted by [name] it was assumed for the power analyses that the average maternal sensitivity score at baseline is 3 with a standard deviation of 0.9. Mothers will be tested both at baseline (T0) and at follow-up (T1). The primary comparison of COS-P and CAU will be adjusted for baseline scores. In the power analysis we will assume a test-retest correlation of 0.5. Ignoring clustering due to treatment groups in the data a sample of 200 dyads would provide 90% power to detect a treatment effect of around 0.40. The final statistical analysis will take clustering into account, but as there are not prior studies to pin down the intra-group effect a conservative approach will be employed. To accommodate this we will aim for having 250 dyads in the final analysis, which is deemed more than sufficient to handle any plausible clustering effect. A likely drop-out for 20% (either during the intervention period or at follow-up) brings the final sample size to 314 at time of randomization. Due to the nature of the trial there are no planned interim analyses or early stopping rules.

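### The lead model for maternal sensitivity is valid but omits infant age at T0 and risk condition, two baseline variables already collected that could add a little precision

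*Protocol article*

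**What the plan says.** Under Statistical methods, the primary comparison is "linear regression of maternal sensitivity at T1 on treatment group adjusted for baseline maternal sensitivity", with GEE for clustering. "A two sided test with a 5% significance level will be employed".

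The same paragraph plans two effect estimates: (a) adjusted for the T0 value of sensitivity, and (b) adjusted for the family characteristics. It ranks them: "Both will be reported but the value a will be considered the important".

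The family characteristics are not listed again at that point. The natural referent is the section Background information and control variables, which begins "Information about risk condition (infant social withdrawal, maternal depression, or both), infant gender and infant age at referral". It goes on to parental age, education, employment, depression history, attachment style, personality dysfunctioning, substance use, smoking and adverse childhood experiences, among others.

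The Measures section places the two assessments as follows: "At baseline (T0) when the infant is 2–12 months old and at follow-up (T1), when the infant is 12–16 months".

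Risk condition returns in the heterogeneity analysis, done by "including an interaction term between group membership and family type" in the regression planned for the primary analysis, with three family types. The Randomization section describes blocks of random size with 2:1 allocation and names no stratification factor.

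**The concern.** Two baseline variables have a better claim than the rest to a place in the lead model.

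- **Risk condition.** The Background section reports that depressed mothers are less sensitively attuned to their infants, so the document itself links this variable to the outcome. The heterogeneity analysis already treats the three family types as potential effect modifiers, and an interaction term would normally bring their main effects with it.
- **Infant age at T0.** T0 sensitivity is the only covariate in the lead model, and it is measured at different infant ages and so at different distances from T1. The sample-size section nevertheless assumes a single T0–T1 correlation of 0.5.

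Randomisation is not stratified on either variable, so some chance imbalance between arms is to be expected. Estimate (b) adjusts for both, but it is ranked second and mixes them with a long list of survey variables. What is at stake is some precision in the estimate the plan calls the important one.

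**Working it through.** **Inputs from the protocol article.** Sample size: "the average maternal sensitivity score at baseline is 3 with a standard deviation of 0.9"; T0–T1 correlation 0.5; 90% power with 200 dyads for an effect of around 0.40, clustering ignored; 250 dyads in the final analysis; 20% drop-out; 314 randomised. Randomization: 2:1. Two-sided 5% test.

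**Step 1: reproduce the plan's own figure.**
Baseline-adjusted SD = 0.9 × √(1 − 0.5²) = 0.779.
At N = 200 and 2:1 (about 66.7 and 133.3 dyads), SE = 0.779 × √(1/66.7 + 1/133.3) = 0.779 × 0.150 = 0.117.
Difference detectable with 90% power = (1.960 + 1.282) × 0.117 = 0.379, in line with the stated value of around 0.40. Power at exactly 0.40 raw points is 92.8%.
The article does not say whether 0.40 is in raw or SD units. Read as 0.40 SD (0.36 raw), power is 90.4% with 1:1 and 86.9% with 2:1 allocation.
Drop-out: 250/0.8 = 312.5, so 313 against 314 stated.
The sizing therefore agrees with a model adjusted for T0 sensitivity alone.

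**Step 2: infant age at T0 on the recruitment schedule.**
EPDS screening is at 2 months; ADBB is at 2, 4 (first-time mothers only) and 8 months; the T0 visit follows 10–20 days later. T0 therefore falls near 2.5, 4.5 or 8.5 months, inside the eligibility limits of 2–12 months. The gap to T1 runs from about 12 − 8.7 = 3.3 months to about 16 − 2.3 = 13.7 months.

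**Step 3: chance imbalance in risk condition.**
The recruitment section expects 113 of 314 families (36%) from the ADBB route. With 250 analysed as 167 and 83, the SE of the between-arm difference in that share is √(0.36 × 0.64 × (1/167 + 1/83)) = 0.064, a 95% range of about ±13 percentage points (simple randomisation, overlap between routes ignored).

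**Step 4: gain from adding the two variables.**
Let R² be the share of residual variance they explain beyond T0 sensitivity. The documents give no value, so the range below is assumed. Residual SD = 0.779 × √(1 − R²). Power is for a raw difference of 0.40 with 2:1 allocation, clustering ignored as in the plan's own calculation.

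| Assumed R² | SE ratio | Detectable difference, N = 200 | Power, N = 200 | Power, N = 250 |
|---|---|---|---|---|
| 0 | 1.000 | 0.379 | 92.8% | 96.9% |
| 2% | 0.990 | 0.375 | 93.3% | 97.2% |
| 5% | 0.975 | 0.369 | 94.0% | 97.5% |
| 10% | 0.949 | 0.360 | 95.0% | 98.1% |
| 20% | 0.894 | 0.339 | 96.9% | 99.0% |

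In equivalent sample size, 250/(1 − R²) − 250 gives about 5, 13 and 28 families for R² of 2%, 5% and 10%.

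**Step 5: cost in degrees of freedom.**
Age as a linear term takes one and three-level risk condition two. At N = 250 the residual degrees of freedom fall from 247 to 244, and √(247/244) = 1.006, about 0.6% of the SE. Break-even R² is about 3/247 = 1.2%.

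**The case against.** The strongest reply is that nothing here is wrong. Regression on arm and the baseline value of the outcome is a standard primary model. With no stratification factor named, the design creates no obligation to adjust for risk condition. Chance imbalance is already reflected in the confidence interval, and the trial was sized for this model. The covariates are not missing from the plan either, since estimate (b) is also prespecified and reported. Preferring the smaller model is legitimate, and refinements of this kind are often settled in the detailed analysis plan that the article promises. All of this stands, and it limits the point to efficiency.

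Two stronger readings are tempting. From the age limits alone a reader might infer that T0 can fall at any age from 2 to 12 months and that the gap to T1 runs from 0 to 14 months. The recruitment schedule does not support that: T0 clusters near three ages, and the gap is about 3 months at the shortest. Since 201 of 314 families (64%) are expected through the EPDS route, most T0 visits should fall near 2.5 months. Age is thus partly tied to risk condition, which may shrink the joint gain.

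A reader might also infer that a given T0 score means something different at different infant ages. The article does not say so; it describes the coding system as validated from infancy to adolescence.

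The reply leaves one thing unanswered. Estimate (b) is ranked second and carries many further variables, so it does not do the work of a lead model with these two covariates.

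**Conclusion.** A minor point that holds as an efficiency improvement. The lead model omits two collected baseline variables that plausibly predict the outcome. With an assumed partial R² of 2–10%, including them lowers the SE by about 1–5% before the 0.6% degrees-of-freedom cost. Power rises by about 0.5–2 points at 200 dyads and about 1 point or less at the planned 250. Below a partial R² of about 1.2% nothing is gained. These figures rest on an SD of 0.9, a T0–T1 correlation of 0.5, 0.40 read in raw units, 2:1 allocation and no clustering.

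A reader might go further and infer that the primary estimate is biased, the test invalid or the trial underpowered because of the omission. The documents do not support any of these: allocation is random and unstratified, and the stated sizing reproduces with T0 adjustment alone. That precision is actually lost is plausible, but the documents cannot show it, because they give no figure for how well either variable predicts T1 sensitivity beyond T0 sensitivity.

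**What to change.** Prespecify the primary model as T1 maternal sensitivity on arm, T0 sensitivity, infant age at T0 and risk condition in three levels (infant withdrawal only, maternal depression only, both), with the clustering method unchanged. Keep the long-list estimate (b) as supportive, and name its covariates there. The heterogeneity analysis then adds only the interaction to a model that already holds the family-type main effects.

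The cost is one sentence and three degrees of freedom. No new data are needed: both variables are tied to eligibility, so they should be known for practically every randomised family, and age at T0 follows from the date of birth and the visit date. The change should be fixed in the statistical analysis plan before any outcome data are seen by arm.
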